#### **6.3.4 Replacement Policy**

Withdrawn subjects will not be replaced.

## **7 STUDY PRODUCT**

### **7.1 Study Medication Supply**

Reconstitution of each taliglucerase alfa vial (212 units) with sterile water for injection (5.1 mL) yields a final volume of 5.3 mL human taliglucerase alfa (40 U/mL), which provides a withdrawal volume of 5.0 mL (200 units). The solution must be mixed gently until clear.

### **7.2 Description of Study Product**

Human taliglucerase alfa is a purified recombinant, plant cells-expressed glucocerebrosidase, which is described in detail in the Investigator Brochure.

Each 200 unit vial contains the following lyophilized contents:

212 units of taliglucerase alfa

195 mg mannitol

35 mg sodium citrate

0.53 mg polysorbate 80, NF

### **7.3 Description of Comparator Product**

Not applicable.

### **7.4 Study Drug Administration**

For initial infusions in all subjects, taliglucerase alfa will be administered at a rate of 1.2 mL/min over 2 hours. The tolerability of the infusion will be determined by signs and symptoms during the infusion for one hour after the infusion in the clinic and by telephone contact the day after the infusion. If this rate of infusion is well tolerated, the rate of infusion may be increased up to 2.25 mL/min to deliver the 135 mL volume over one hour for all subsequent dosing after discussion with the Medical Director. The infusion rate may be adjusted according to individual subject symptoms and signs (see Section 13.2, Appendix 2).

### **7.5 Packaging and Labeling**

Lyophilized drug powder is stored in 13.5 mL borosilicate glass (Type 1) bottles (Forma Vitrum AG, Hungary). Lyophilization stoppers (Helvoet Pharma, Belgium) composed of two-leg brombutyl rubber are sealed with aluminum Snap Caps and polypropylen discs (Helvoet Pharma, Belgium).

The label is in Appendix 1.

### **7.6 Conditions for Storage and Use**

The product is stored at 2-8°C (36-46°F).

### **7.7 Method of Assigning Subjects to Treatment Groups**

This is a randomized study and all subjects will be assigned to treatment with taliglucerase alfa 30 or 60 units/kg. A unique screening number (formatted as xxS5yyy [x: site number, 5: protocol number, y: subject number]) will be assigned to each screened subject. Once a subject is eligible for randomization, including successful completion of screening and prior to visit 1, a subject randomization number will be generated that will include the site and subject number (formatted as xx-5yyy [x: site number, 5: protocol number, y: randomization number]). Subjects will be randomized to one of the two treatment groups (30 units/kg or 60 units/kg) based on a centralized computer-generated randomization code.

### **7.8 Dispensing, Compliance and Accountability**

Protalix will provide drug accountability forms to assist the pharmacist in maintaining current and accurate inventory records covering receipt, dispensing, and the return of investigational drug supplies. When a shipment is received, the pharmacist will verify the quantities received and return the acknowledgment to the study monitor or designee. The pharmacist investigational drug accountability record includes the identification of the person to whom the drug is dispensed, the quantity and the date of dispensing and any returned or unused drug. This record is in addition to any drug accountability information recorded on the Case Report Form (CRF). These records will be readily available for inspection by a monitor or Protalix audits and are open to regulatory authority inspection at any time.

The investigator is responsible for maintaining accountability for the receipt, dispensing, and return of all study medication.

### **7.9 Prior and Concomitant Therapy**

Medications having the potential to interfere with the evaluation of efficacy are excluded throughout the trial.

The following medications are strictly prohibited during the study:

- Zavesca® (miglustat)
- Ceredase® (alglucerase)
- Cerezyme® (imiglucerase)

The following medications are allowed and expected during the study:

- Treatments for hypersensitivity, anaphylaxis, or anaphylactoid reactions; e.g., epinephrine, norepinephrine, glucagons, albuterol
- Treatments for anemia; e.g., iron, folic acid, vitamin B12
- Treatments for bone disease; e.g., biphosphonates

- Analgesics; e.g., nonsteroidal anti-inflammatory drugs (note: aspirin may be contraindicated due to its effects on platelets and risk for bleeding)

## **8 EFFICACY AND SAFETY ASSESSMENTS**

### **8.1 Efficacy Variable(s)**

- The primary efficacy variable is median percentage and the interquartile range for change from baseline in haemoglobin
- Secondary efficacy variables are:
  - Percent change from baseline in chitotriosidase or CCL18
  - Percent change from baseline in spleen and liver volume (see Appendix 4)
  - Percent change from baseline in platelet count
- Exploratory endpoints are:
  - Change in height and weight
  - Change in Tanner Stage
  - Change in bone age by X-ray of left hand and wrist
  - Change in bone density by DEXA
  - Occurrence of bone crises
  - Quality of Life using the Child Health Questionnaire™ (CHQ) PF-28 (valid for subjects aged 5 to 18 years)

### **8.2 Safety Variables**

The safety of taliglucerase alfa will be assessed by clinical laboratory, echocardiography, anti-taliglucerase alfa antibodies, and adverse events.

#### **8.2.1 Clinical Laboratory**

- Haematology: complete blood count; total white blood cell count, differential count (neutrophils, lymphocytes, monocytes, eosinophils and basophils), red blood cells, (hemoglobin, hematocrit, mean corpuscular volume, mean corpuscular hemoglobin and mean corpuscular hemoglobin concentration), and platelets
- Biochemistry: sodium, potassium, glucose, blood urea nitrogen, creatinine, calcium, phosphate (inorganic), uric acid, total protein, albumin, bilirubin (total), alkaline phosphatase, aspartate transaminase, alanine transaminase, gamma-glutamyl transferase, lactate dehydrogenase
- Urinalysis: dipstick for presence of glucose, ketones and protein

#### **8.2.2 Echocardiography**

Doppler Flow Echocardiography is a noninvasive imaging modality for detecting pulmonary hypertension by evaluating the grade of tricuspid insufficiency, a condition potentially associated with Gaucher disease.

### **8.2.3 Anti-Taliglucerase alfa Antibodies**

Anti-taliglucerase alfa antibodies, including neutralizing antibodies in subjects having a positive antibody response, will be assessed using a validated analytical method.

### **8.2.4 Adverse Events**

#### **8.2.4.1 Adverse Events (AE) and Serious Adverse Events (SAE)**

An adverse event (AE) is any untoward medical occurrence in a subject participating in a clinical trial. An adverse event can be any unfavorable and unintended sign, symptom or disease temporally associated with the use of the study medication, whether or not considered related to the study medication. AEs will be collected from the start of treatment until 30 days following the final visit dose. Any events occurring prior to treatment will be recorded on the medical history page with the event name and onset date and end date if not continuing. Pre-existing, known clinically significant conditions observed at screening should be recorded as medical history.

This definition also includes accidental injuries, reasons for any change in medication (drug and/or dose) other than planned titration, reasons for admission to a hospital, or reasons for surgical procedures (unless for minor elective surgery for a pre-existing condition). It also includes adverse events commonly observed and adverse events anticipated based on the pharmacological effect of the study medication. Any laboratory abnormality assessed as clinically significant by the Investigator must be recorded as an adverse event.

A treatment emergent adverse event is any adverse event occurring after start of study medication and within the time of residual drug effect, or a pre-treatment adverse event or pre-existing medical condition that worsens in intensity after start of study medication and within the time of residual drug effect.

Adverse events should be recorded as diagnoses, if available. If not, separate sign(s) and symptom(s) are recorded. One diagnosis/symptom should be entered per record.

Note that death is not an event, but the cause of death is. An exception is the event of sudden death of unknown cause. Note that hospitalization is not an event; however, the reason for hospitalization is. Procedures are not events; the reasons for conducting the procedures are. In general, only the reason for conducting the procedure will be captured as an adverse event. However, if deemed necessary by the Investigator, a procedure can be captured along with the reason for conducting the procedure.

An overdose or medication error is not an adverse event unless it is temporally associated with an unfavourable or unintended sign or symptom.

Each AE is to be classified by the investigator as serious or non-serious. A serious adverse event (SAE) is any untoward medical occurrence or effect that occurs at any dose:

- Results in death
- Is life-threatening (i.e., an immediate risk of death)
- Requires in-patient hospitalization or prolongation of existing hospitalization
- Results in persistent or significant disability/incapacity
- Is associated with a congenital anomaly/birth defect
- Is an important medical event

An adverse event caused by an overdose or medication error is considered serious if a criterion listed in the definition above is fulfilled.

Important adverse events that may not result in death, may not be life-threatening, or do not require hospitalization may be considered serious when, based upon appropriate medical judgment, they may jeopardize the subject's safety or may require medical or surgical intervention to prevent one of the outcomes listed above.

Serious adverse events also include any other event that the investigator or sponsor judges to be serious or which is defined as serious by the regulatory agency.

The investigator is to report all directly observed adverse events and all adverse events spontaneously reported by the trial subject using concise medical terminology. In addition, each trial subject will be questioned about adverse events. The question asked will be "Since you began taking the study medication, have you had any health problems?"

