### **9.2.2 Visit 1 (Baseline, Day 1)**

1. Assign to randomized treatment group
2. Concomitant medications
3. Physical examination including weight and height
4. MRI or ultrasound for spleen and liver volume
5. Echocardiography (for tricuspid insufficiency gradient)
6. Clinical laboratory tests
  - Blood platelet count and hemoglobin (local)
  - Haematology
  - Biochemistry
  - Urinalysis
  - Anti-taliglucerase alfa antibody
  - Biomarkers: chitotriosidase or CCL18
  - Mutation analysis
7. Left hand and wrist X ray for bone age
8. Tanner Stage

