9. DEXA
10. Quality of Life (CHQ PF-28)
11. Taliglucerase alfa infusion

---

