9. DEXA
10. Taliglucerase alfa infusion

Perform the following procedures for taliglucerase alfa dosing:

- Observe the subject clinically for a minimum of 1 hour after dosing
- Evaluate vital signs every 30 minutes
- Evaluate the injection site.

Protocol Number PB-06-005

Protalix Ltd.  
April 28, 2010

---

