### **13.4.2 Magnetic Resonance Imaging (MRI) data**

Each subject enrolled in this trial will have 2 MRI timepoints during the course of the trial at Baseline and Month 12.

For each timepoint, the same set of T1 and T2-weighted MRI sequences will be acquired. These sequences will be defined based on their equipment and abilities to provide sufficient image quality and contrast for organ (spleen and liver) detection and quantification, and also full spleen and liver coverage in Gaucher subjects. No contrast agent will be used. If baseline MRI cannot be obtained, organ volumes can be obtained by ultrasound technology with approval of the Medical Director.

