**13.4.4.2 Subject Sedation**

Pediatric subjects may require sedation in order to obtain the high quality images required. Sites may use standard sedation protocols approved by the institution.

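### AE rules conflict for events after consent but before the first dose, and the promised 30 days after the last dose have no scheduled contact for completers outside the extension

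*Protocol*

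**What the plan says.** Section 8.2.4.1 sets both ends of the collection window: "AEs will be collected from the start of treatment until 30 days following the final visit dose". For anything earlier it says: "Any events occurring prior to treatment will be recorded on the medical history page". It makes no exception for serious events or for events caused by a study procedure.

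Procedures do take place before the first dose. Under Visit 1 (Section 9.2.2), item 4 is "MRI or ultrasound for spleen and liver volume", and the first infusion is item 11. Appendix 4 (Section 13.4.2) states that each subject "will have 2 MRI timepoints during the course of the trial at Baseline and Month 12", and Section 13.4.4.2 adds: "Pediatric subjects may require sedation in order to obtain the high quality images required".

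At the other end, the flow chart (Section 9.1) and the visit list stop at Visit 28, Week 52 ± 7 days. That visit includes "10. Taliglucerase alfa infusion" and at least one hour of clinical observation. No later visit or call is listed. The only telephone call in the visit list is the one on the day after the Visit 1 infusion.

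**The concern.** Two things look wrong.

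First, if a child has a serious sedation complication at the baseline scan, the collection sentence sends it to medical history. Other sentences in the same part of the protocol treat it as an AE. The site cannot tell which rule governs, so it cannot tell whether the 24-hour SAE rule in Section 8.2.4.2 applies.

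Second, the protocol sets a 30-day window after the last dose but schedules nothing to cover it.

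Safety is a stated objective (Section 5), the study is described as one of the first paediatric exposures (Section 6.2), and only 10 subjects are planned, so each event carries weight. These are matters for the protocol. A statistical analysis plan can decide how to tabulate events, but it cannot recover events that were never collected.

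**Working it through.** The plan gives no figure to reproduce. The check sets the rules side by side and then does the day arithmetic.

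**Start of the window**

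Text pointing to exclusion of pre-dose events:
- Section 8.2.4.1: collection starts with treatment, and earlier events go to the medical history page.
- Section 8.2.4.1: the SAE definition is tied to dosing, and the scripted question asks only about the time since study medication began.
- Section 9.1: the AE row of the flow chart is blank at Screening.

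Text pointing to inclusion:
- Section 8.2.4.1: an AE is any unwelcome medical event in a trial participant, related to the drug or not.
- Section 8.2.4.1: the treatment-emergent definition includes AEs that began before treatment and later worsened, so it presupposes that such AEs exist.
- Section 8.2.4.1: the investigator or sponsor may judge any other event serious.
- Section 8.2.4.2: every AE arising while the study runs is to be reported, drug-related or not, and every SAE within 24 hours.

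The two sets are not reconciled. What differs in practice is the data captured. A medical history entry has event name, onset date and end date. An AE entry under Section 8.2.4.2 also has intensity, seriousness and relationship to the drug.

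The exposed procedure is narrow. Of the two MRI timepoints, only the baseline one can precede the first dose. The Month 12 scan falls inside the AE window.

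**End of the window**

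Inputs: first dose on Day 1 and final dose at Week 52 ± 7 days (Section 9.2); 30 days after the final dose (Section 8.2.4.1); 10 subjects (Section 6.1).

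- Final dose: Day 1 + 52 × 7 = Day 365, range 358 to 372.
- Stated end of collection: 365 + 30 = Day 395, range 388 to 402.
- Last scheduled contact: Day 365, range 358 to 372.
- Share of the window without a scheduled contact: 30/(364 + 30) = 30/394 = 7.6%.
- Upper bound on time: 10 × 30 = 300 subject-days, if all 10 complete and none enters the extension.
- Infusions: every two weeks from Week 0 to Week 52 gives 52/2 + 1 = 27. Visit numbers run to 28, because Visits 21 to 27 are paired with only six weeks. On either count, the last infusion is the only one with no later scheduled visit.

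**Illustration under assumptions**

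The Introduction reports 137 AEs, 28 of them treatment-related, among 32 patients in a 38-week study (PB-06-001). Assume that all 32 were followed for 38 weeks and that the rate carries over to this population:
- Patient-days: 32 × 38 × 7 = 8,512.
- Rate: 137/8,512 = 0.016 per day.
- AEs arising in 300 subject-days: about 4.8, or about 2.4 at half that rate.
- Treatment-related AEs: 28/8,512 × 300 = about 1.0.

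These are events that would arise, not events that would be lost, since some would be reported spontaneously. The same study had no SAEs.

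**The case against.** The other side has good arguments, and several limit the point.

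- A reader might infer that a pre-dose sedation complication is by rule neither an AE nor reportable within 24 hours. No sentence says so, and the inclusive text listed above says otherwise. What stands is an unresolved conflict, not a settled exclusion.
- A reader might infer that such events vanish from the data. They do not. They are recorded on the medical history page, though without seriousness or causality.
- Sedation is conditional, and ultrasound may replace MRI if the baseline scan cannot be obtained (Section 13.4.2). This stands and keeps the exposure small.
- Screening on Day −25 ± 10 could suggest a gap of up to 35 days from consent. That does not measure the sedation hazard. Screening consists of history, examination and laboratory tests, and the scan is a Day 1 procedure.
- A reader might conclude that the final 30 days cannot be observed at all. That is too strong. Spontaneous reports are recorded, and known events are followed until resolved or stable (Section 8.2.4). Section 6.3.3 provides attempted follow-up of at least 30 days for early discontinuers, and some subjects will be seen in the extension.

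These arguments do not cover a subject who completes Visit 28 and stays out of the extension. Section 6.3.3 does not apply to that subject. The extension depends on eligibility and on the drug not being on the market (Section 6.1). Following a known event to resolution does not detect a new one. Starting routine AE collection at first dose is a defensible choice, but it needs a clear rule for serious and procedure-related events before that.

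**Conclusion.** The point holds in two limited parts.

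Sections 8.2.4.1 and 8.2.4.2 give conflicting signals on events after consent and before the first dose. A serious procedure complication in that interval therefore has no clear route to AE recording or expedited reporting. In practice this concerns at most one possibly sedated scan per subject. It assumes that the baseline scan is done before the infusion, as the order of the Visit 1 list implies.

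Separately, completers who do not enter the extension have no scheduled contact in the 30 days for which collection is promised. That is 7.6% of the stated window by calendar time and at most 300 subject-days. The percentage is a share of time and should not be read as a share of events lost.

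The effect is on the completeness of the safety data. The efficacy analysis is untouched.

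**What to change.** Reconcile Sections 8.2.4.1 and 8.2.4.2 with one rule: SAEs, and any event related to a protocol procedure including sedation, are collected and reported from signed consent. Record them with the full AE fields and tabulate them separately from treatment-emergent events. Other pre-dose events can stay on the medical history page. Bring the scripted question and the AE row of the flow chart into line.

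Add to Section 9.2 and the flow chart a telephone AE contact 30 days after the last infusion (nominally Day 395) for every subject not seen in the extension by then.

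The cost is at most one call per subject, so at most 10 calls, one change to the case report form rules, and a few more non-drug events to record. Treatment and dosing do not change.

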#### **8.2.4.2 Procedures for Assessing, Recording, and Reporting Adverse Events and Serious Adverse Events**

Throughout the duration of the study, the Investigator will closely monitor each subject for evidence of drug intolerance and for the development of clinical or laboratory evidence of adverse events. All adverse events (expected or unexpected) which occur during the course of the study, whether observed by the Investigator or by the subject, and whether or not thought to be drug-related, will be reported and followed until resolution or until they become stable.

The description of the adverse event will include description of event, start date, stop date, intensity, if it was serious, relationship to test drug, change in test drug dosage, if the subject died, and if treatment was required.

Events will be coded to one of the following intensity categories below:

| Severity | Definition                                                                |
|----------|---------------------------------------------------------------------------|
| Mild     | Awareness of signs or symptoms, but no disruption of usual activity       |
| Moderate | Event sufficient to affect usual activity (disturbing)                    |
| Severe   | Event causes inability to work or perform usual activities (unacceptable) |

Events will be coded into one of the following causality categories as defined below:

| Category  | Definition                                                                                                                                                                                                                                            |
|-----------|-------------------------------------------------------------------------------------------------------------------------------------------------------------------------------------------------------------------------------------------------------|
| Unrelated | Clearly and incontrovertibly due only to extraneous causes, and does not meet criteria listed under possible or probable.                                                                                                                             |
| Unlikely  | Does not follow a reasonable temporal sequence from administration. May have been produced by the subject's clinical state or by environmental factors or other therapies administered.                                                               |
| Possible  | Follows a reasonable temporal sequence from administration, but may have been also produced by the subject's clinical state, environmental factors or other therapies administered.                                                                   |
| Probable  | Clear-cut temporal association with administration with improvement on cessation of investigational medicinal product or reduction in dose. Reappears upon rechallenge. Follows a known pattern of response to the investigational medicinal product. |

Adverse events with the causality assessed as unrelated or unlikely are categorized as not related to study medication.

Adverse events with the causality assessed as possible or probable are categorized as related to study medication and are called adverse drug reactions.

All SAEs must be reported **immediately (no more than 24 hours after becoming aware of the event)**. The investigator must complete the eCRF SAE Report and contact the Safety Monitor ([name]) IMMEDIATELY to [contact], according to the Serious Adverse Event Report Form Instructions.

